### Investigational product

The investigational product to be used in this trial is a MNP (MixMe WHO) produced by the DSM Company and distributed routinely by the United Nations Children’s Fund and the World Food Programme (contains 10 mg of iron). For our study purposes the iron concentration will be altered and we will use products containing 12 mg, 6 mg and 0 mg iron/sachet (daily dose). Each sachet will consist of the micronutrient powder described in Table 1. All sachets will look the same, which will help ensure that field workers, study nurses, participants and the principle investigator are blinded.

**Table 1 Tab1:** Vitamin and mineral content in a single daily dose of the micronutrient powder (sachet)

Micronutrients	Dose/day
Vitamin A (ug RE)	400
Vitamin D (ug)	5
Vitamin E (mg)	5
Vitamin C (mg)	30
Thiamine (B_1_) (mg)	0.5
Riboflavin (B_2_) (mg)	0.5
Niacin (B_3_) (mg)	6
Pyridoxine (B_6_) (mg)	0.5
Cobalamine (B_12_) (ug)	0.9
Folate (ug)	150
*Iron (encapsulated ferrous fumarate) (mg)*	*12 or 6 or 0*
Zinc (mg)	4.1
Copper (mg)	0.56
Selenium (ug)	17
Iodine (ug)	90

Children additionally participating in the sub-study will receive a single dose of 2 mg iron, in the form of ^57^Fe-enriched ferrous sulphate, at the day of enrolment into the sub-study.

### Laboratory evaluations

#### Blood samples

In the *venous blood samples* collected on Days 0, 49 and 84 the following parameters will be assessed: full haematology panel (using a Medonic M^20M^ GP); ferritin, soluble transferrin receptor (sTfR), serum iron, transferrin, transferrin saturation (TSAT), c-reactive protein (CRP), alpha 1-acid glycoprotein (AGP) (using a fully automated biochemistry analyser Cobas Integra 400 plus); and hepcidin (using the Hepcidin-25 (human) EIA Kit (Bachem) and a Thermo Scientific Multiskan FC Microplate Photometer). Red blood cells (RBCs) will be lysed for measurement of riboflavin status by the erythrocyte glutathione reductase activation coefficient (EGRAC) test.

*Ex vivo* growth of *P. falciparum* will be assessed in washed RBCs using a field-ready 96-well plate method and a basic flow cytometry readout (with the BD Accuri CSampler) in which parasitized RBCs (pRBCs) are identified by DNA dye SYBR green I (Life Technologies). Briefly, cultures will be seeded into RBCs from study participants as rings at 0.5 % initial pRBCs and 1 % haematocrit in triplicate into 96 well plates and maintained for 96 h. Parasite growth rates will be determined by dividing final parasitaemia at 96 h by initial parasitaemia at 0 h [17].

*Ex vivo* growth of sentinel bacteria (*Staphylococcus aureus*, *Staphylococcus epidermidis*, *E. Coli* and *Salmonella* Typhimurium) in participant serum will be assessed by optical density plots confirmed by baseline and end-point colony counts using the cell culture counting facility of a Thermo Scientific Multiskan FC Microplate Photometer [18].

From the Day 0 whole blood samples genotyping for haemoglobinopathies will be done using haemoglobin electrophoresis and DNA will be extracted using the salting out method to look at genetics of iron metabolism. Known genetic risk factors to be assessed include alpha-thalassemia, glucose-6-phosphate dehydrogenase deficiency and sickle traits. Furthermore, putative functional and key tagging variants in iron regulatory and inflammatory pathways will be screened. Much of this will be available from the Illumina Infinium Human Exome Bead Chip (Exome Chip). A specific ‘iron chip’ may be developed.

In addition to all the analyses done with the venous blood samples for the main study (Days 0, 49 and 84), the isotopic ratio will be measured in RBCs of sub-study participants using an Inductively Coupled Plasma Mass Spectrometer (ICP-MS). In the additional blood sample taken in this subgroup of participants on Day 168, isotopic composition, full haematology, ferritin, sTfR, serum iron, transferrin, TSAT, CRP and AGP will be measured as described above.

In the weekly *finger prick blood samples* Hb using a HemoCue 301 and a RDT (SD BIOLINE Malaria Ag P.f, Standard Diagnostics, Inc.) will be directly performed in the field. In case of a positive RDT a blood film will be prepared and read at the laboratory in Keneba. Hepcidin collected into a BD microtainer® will be measured in the laboratory in Keneba as described above for venous blood.

#### Stool samples

Samples at Days 0, 14 and 84 will be collected in a sterile container with a tight, screw top lid that includes an Anaerocult® sachet (Merck, Darmstadt, Germany) to create an anaerobic environment. The samples will be aliquoted and frozen at -20 °C. Calprotectin (fCAL ELISA, Bühlmann Laboratories AG, Schönenbuch, Switzerland) will be assessed using ELISA methods. The gut microbiota composition will be assessed using 16S rRNA analysis and qPCR on enterobacteriaceae and target commensal bacteria.

### Data entry and handling

Field data will be directly entered into handheld devices (Samsung Galaxy Tab 3 SM-T111) using the Cellica Database Software and synced into the database via a direct secure connection over the 3G mobile network. Field measurements/readings will additionally be entered into a separate physical data collection sheet at each measurement station. These data will be entered by the data entry clerks to serve as the second entry. A double entry verification system is executed to detect discrepancies between the two entries. Discrepancies will be sent as queries to the Principal Investigator for resolution.

### Sample size

This is a non-inferiority trial to evaluate efficacy and the primary endpoint is Hb concentration (measured using a Medonic haematology analyser in the laboratory) at day 84. Based on a SD of 1.15 g/dL of the mean Hb value of children at 24 week of age, from a previous trial conducted at Keneba [19], a sample size of 131 participants in each of the three arms is required using a 1-sided α of 2.5 and a Bonferroni correction to adjust for multiple testing. A total sample size of 393 children followed up for 12 weeks, with a drop-out of less than 15 %, will provide 80 % power to establish that:arm B is non-inferior to arm A on the primary endpoint (Hb concentration at Day 84) defined as the upper 98.3 % confidence limit for the difference in mean Hb being not greater than 0.5 g/dL (non-inferiority margin), the smallest value considered to be of public health relevancearm C is non-inferior to arm A at the same level as abovearm C is non-inferior to arm B at the same level as above

For the sub-study, the power calculation for iron absorption is based on the data from Fomon et al. [20] in infants. Twenty subjects per group are required to resolve a difference in absorbed iron of 0.080 mg/d between the control and intervention period, based on a SD of 0.13 mg/d (paired t-test). The between group difference that we estimate being able to resolve is 0.12 mg/d absorbed iron (unpaired *t*-test). Lower variability is expected in the calculated k_abs_ values, which are independent from Hb, body weight, and iron status, the main contributors to variability in the calculation of iron absorption. Considering attrition due to the long time span of at least 7 months between recruitment (administration of stable isotope dose) and participation in the main study, 30 subjects per group will be recruited.

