### Study objectives

The *primary objective* is to evaluate whether weekly hepcidin-based screen-and-treat at 12 mg iron/day, screen-and-treat at 6 mg iron/day and 12 mg iron/day universal supplementation for 12 weeks are all non-inferior. The primary endpoint is Hb (measured using a Medonic haematology analyser in the laboratory) at day 84. Secondary endpoints related to the primary objectives are:i)Proportion of anaemia (Hb < 11 g/dL) at Day 84;ii)Proportion of iron deficiency (sTfR/logFerritin ratio > 3.2 or > 2.0 in the presence of inflammation (CRP > 5 mg/L) and ferritin < 12 μg/L or < 30 μg/L in the presence of inflammation) at Day 84;iii)Proportion of iron deficiency anaemia (Hb < 11 g/dL and sTfR/logFerritin ratio > 3.2 or > 2.0 in the presence of inflammation and ferritin < 12 μg/L or < 30 μg/L in the presence of inflammation) at Day 84;iv)Ferritin (only participants without inflammation), soluble transferrin receptor (sTfR), transferrin and transferrin saturation (TSAT) at Day 84.

The *secondary objectives* are the evaluation of i) the feasibility of adopting a hepcidin-based screen-and-treat approach to iron supplementation in young children (number of weeks supplemented with iron); ii) beneficial effects with screen-and-treat with respect to maternal reporting of child illness and safety indices (inflammatory and immune activation markers, faecal gut inflammation markers, gut microbiota, *ex-vivo* bacterial and *P. falciparum* growth); and iii) overall iron absorption over the 12 week supplementation period in the three study arms (sub-study).

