### Statistical analysis

The primary haemoglobin outcome (measured using a Medonic haematology analyser in the laboratory) at day 84 will be tested for non-inferiority by performing a per-protocol analysis with a 5 % significance level, adjusted using the Bonferroni correction to account for three main comparisons. We will also repeat the main analysis using the intention-to-treat population as a confirmatory analysis.

Secondary outcome analysis of continuous variables (ferritin, sTfR, transferrin, TSAT, CRP, AGP, calprotectin, *ex-vivo* growth, gut microbiota, number of weeks supplemented) will be done using mixed-effect models with individuals treated as a random effect, and secondary outcome analysis of categorical variables (anaemia, ID and IDA) will be modelled using mixed-effect logistic regression. Interactions between study arm and time in the study will be investigated.

Morbidity data will be analysed using mixed-effect models controlled for possible confounders.

Exploratory analysis will be performed using serum iron.

All data will be analysed using Stata v12.1 (StataCorp, LP, USE, http://www.stata.com) and statistical significance will be defined as *p* < 0.05, unless stated otherwise.

In the sub-study, the linear regression of log^57^A^t^ (^57^A^t^ = abundance at time t) against time will be calculated for each subject belonging to the three different groups for the period of Day 0 to Day 84 (with a midpoint sample at day 49). The slope (k_abs_) of the regression reflects the absorption of iron per unit of time. The difference in the slopes between the groups will be equivalent to the average iron absorption over time in each group (k_abs_ in groups A, B, and C, respectively).

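### The 80 % power is for each comparison separately at a true difference of zero; for all three at the Bonferroni-corrected level it is about 58 %

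*Protocol article*

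**What the plan says.** The Study objectives section states the primary objective as a single statement about the three regimens: that screen-and-treat at 12 mg, screen-and-treat at 6 mg and "universal supplementation for 12 weeks are all non-inferior".

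The Sample size section gives 131 children per arm, 393 in all, "Based on a SD of 1.15 g/dL of the mean Hb value of children at 24 week of age", "using a 1-sided α of 2.5 and a Bonferroni correction to adjust for multiple testing". It claims 80 % "power to establish that:arm B is non-inferior to arm A on the primary endpoint (Hb concentration at Day 84", the criterion being "the upper 98.3 % confidence limit for the difference in mean Hb being not greater than 0.5 g/dL (non-inferiority margin". C against A and C against B follow as further items at the same level. The loss allowed for is a drop-out below 15 %. The section does not say whether the 80 % is for each item or for the list as a whole, and it gives no assumed true difference between arms.

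The Statistical analysis section says that the primary outcome "will be tested for non-inferiority by performing a per-protocol analysis", with the significance level "adjusted using the Bonferroni correction to account for three main comparisons".

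**The concern.** Read with the objective, the power sentence promises 80 % for a set of three statements that must all be true. A calculation for one two-arm comparison cannot deliver that, because the chance of passing three tests is lower than the chance of passing any one of them. The three tests share arms and so are correlated, but not enough to close the gap.

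Two things are at stake. A reader who takes the sentence at face value will think that the full objective is missed only one time in five when the regimens are truly equal. And the document points two ways on what counts as success: the objective is worded as a conjunction, while a Bonferroni correction is the device for several separate claims. Someone reporting two passes out of three would not know from this text whether the primary objective had been met.

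**Working it through.** **Inputs.** SD 1.15 g/dL, margin 0.5 g/dL, one-sided 2.5 % with Bonferroni correction, drop-out up to 15 %, 131 per arm and power 80 % (Sample size); three comparisons (Sample size and Statistical analysis). The true difference is not stated. Zero is inferred below because it reproduces the plan's figure.

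**Step 1: the plan's own figure.** The level per comparison is 0.025/3 = 0.00833, so z = 2.394; for 80 % power, z = 0.8416.

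n = 2 × 1.15² × (2.394 + 0.8416)² / 0.5² = 110.8, so 111 evaluable per arm.

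111 / 0.85 = 130.6, so 131 per arm, and 3 × 131 = 393. This is an exact match. One-sided 0.025 without correction would give 84, inflated to 99. One-sided 0.0167 would give 94, inflated to 111. Neither matches.

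**Step 2: one comparison.** SE = 1.15 × √(2/n), and power = Φ(0.5/SE − z).

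- n = 111: SE = 0.154, and power is 80.1 %.
- n = 131 (no drop-out): SE = 0.142, and power is 87.0 %.

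**Step 3: all three.** Let D1 = A − B, D2 = A − C and D3 = B − C in observed mean Hb. Each passes if D < 0.5 − z × SE. Since D2 = D1 + D3, the correlations are 0.5 (D1, D2), 0.5 (D2, D3) and −0.5 (D1, D3). Joint power with 111 evaluable at the corrected level is 57.6 % by numerical integration, and 4 million simulated trials agree. The other joint figures below come from the same simulation. True differences are zero throughout.

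| Evaluable per arm | One-sided level | Each comparison | B v A and C v A | All three |
|---|---|---|---|---|
| 111 | 0.025/3 | 80 % | 69 % | 58 % |
| 131 | 0.025/3 | 87 % | 79 % | 70 % |
| 111 | 0.025 | 90 % | 83 % | 76 % |
| 131 | 0.025 | 94 % | 90 % | 85 % |

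The first two rows use the level that the plan fixes. The last two drop the correction, as a strict all-must-succeed rule would allow.

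**Step 4: how the 98.3 % limit is read.** Above it is the upper limit of a two-sided interval (1 − 0.05/3 = 0.983), which agrees with one-sided 0.025/3. Read as a one-sided limit (level 0.0167), power for all three is 70 % with 111 evaluable and 80 % with 131. The latter leaves no room for drop-out and uses twice the level that a corrected one-sided 2.5 % implies, so it does not rescue the sentence as written.

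**Step 5: illustration only.** With an assumed true deficit of 0.1 g/dL and 111 evaluable, power for one comparison is Φ(0.4/0.154 − 2.394), about 58 %. The 0.1 g/dL is not a figure from the document.

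**The case against.** The strongest reply is that the authors meant three separate claims. The correction is for three main comparisons, and the Sample size section lists them one by one at the same level. The abstract's Methods paragraph speaks only of testing the screen-and-treat approaches against universal supplementation, and the Discussion speaks of a single approach being non-inferior. On that reading 80 % is right for each comparison at zero difference, and the chance of showing at least one of B or C non-inferior to A is 80.1 + 80.1 − 68.8, about 91 %. A zero difference is also a usual planning assumption for non-inferiority. For arm B it fits the argument under Hepcidin-guided iron supplementation that children with high hepcidin absorb oral iron poorly. That argument is weaker for arm C.

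Most of this stands. It is also fair that 58 % joins an all-must-succeed rule to a correction that such a rule does not need. What it does not remove is that the objective is worded as a conjunction, and that the power sentence covers the list without saying that 80 % is for each item. Even without the correction, joint power at the planned 111 evaluable is 76 %, below 80 %; it passes 80 % only if losses are smaller (119 evaluable are needed).

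A reader might also infer that the per-protocol primary analysis will take the evaluable number below 111, because the 15 % is described as drop-out. The document does not support that. The article does not define the per-protocol set or what counts as drop-out, which can be left to the full protocol or analysis plan, and the Follow-up section has field workers supervise dosing daily.

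**Conclusion.** The point holds as one of a power statement that does not match the stated objective. The 80 % is the power of each single comparison, given SD 1.15, margin 0.5 g/dL, one-sided 0.025/3, 111 evaluable per arm and a true difference of zero. For all three at that level it is about 58 %, or about 70 % if nobody is lost. If the objective is truly joint and the correction is dropped, the figures are about 76 % and 85 %.

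Three stronger readings are tempting and not supported. First, 131 per arm is not a miscalculation; it reproduces exactly. Second, it does not follow that the trial as a whole has a two-in-five chance of failing: that takes the joint rule and the correction together, and nowhere does the document say that the trial fails if one comparison misses. Third, nothing in the document predicts a true deficit in B or C. Arm A receives at least as much iron by design, but no Hb difference is given, so power at 0.1 g/dL is a sensitivity figure and not a forecast. The correction is worth making, but it is one of wording and consistency and leaves the design intact.

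**What to change.** In the Sample size section, replace the power claim with, for example: *80 % power for each comparison, assuming no true difference, SD 1.15 g/dL and 111 evaluable children per arm; about 58 % to establish all three at the Bonferroni-corrected level.*

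Then reconcile the Study objectives section with the correction in the Sample size and Statistical analysis sections:

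- If three separate claims are meant, say in the objective that each comparison is judged on its own, and keep the correction.
- If one joint claim is meant, say that all three must succeed. The correction is then unnecessary, and the power to quote without it is about 76 % with 111 evaluable and 85 % with 131. Any such change of level should be made without sight of results by arm.

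Power at a small deficit, such as about 58 % per comparison at an assumed 0.1 g/dL, may be added if labelled as illustrative.

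The cost is a few sentences and a less favourable figure for the joint objective. No extra children are asked for. For scale only, 80 % joint power would need 178 per arm (534 in all) with the correction and 140 per arm (420 in all) without it, after 15 % drop-out.

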### The role of hepcidin – the master regulator of iron metabolism

Iron homeostasis, and its distribution within the body, is maintained by regulating absorption of iron through duodenal enterocytes and by controlling the rate of iron recycling through macrophages. Hepcidin is a small peptide hormone that binds to and causes the degradation of ferroportin, an iron export protein highly expressed by enterocytes and macrophages [11]. High levels of hepcidin thereby inhibit absorption of dietary iron and lock iron in macrophages, rapidly depleting serum iron (causing the protective hypoferraemia of the acute phase response) and lowering iron availability for erythropoiesis [12]. An abundance of genetic evidence in humans and experimental animals indicates that the ferroportin-hepcidin interaction is the dominant and non-redundant regulator of iron balance and iron distribution. Regulation of hepcidin is complex – iron accumulation induces hepcidin, providing a negative feedback loop to maintain homeostasis, but hepcidin levels are also increased by inflammatory signals arising during infections. Iron deficiency and erythropoietic drive suppress hepcidin, releasing iron from cellular stores and increasing dietary iron absorption. Importantly, each of these signals is variable, and the balance between them determines hepcidin synthesis. Thus, an iron deficient individual may have high serum hepcidin due to an acute infection, but on the other hand severe anaemia may suppress hepcidin even in the presence of inflammation.

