### Hepcidin-guided iron supplementation

Because hepcidin reports on the balance of iron status and inflammation, and because hepcidin also determines how well oral iron is absorbed [11], low hepcidin levels indicate both a requirement for iron and an ability to utilize it if provided. Individuals with high hepcidin may be iron replete, or inflamed, or both, but will not be able to absorb oral iron efficiently. In our recently published paper this is clearly illustrated in young children, and our results suggest a cut-off of 5.5 ng/mL [14]. As discussed above, iron supplementation may provide limited benefit and be associated with deleterious consequences when given in the presence of inflammation. Therefore, providing an extra decision point (do not give iron unless hepcidin is below a cut-off level) in iron supplementation programs should make them both safer and more efficient. This will permit safe iron supplementation of young children in infectious areas allowing them to reach their full human potential.

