The assumption of homogenous labelling will be assessed by testing the linearity of the slope between Days 0, 49 and 84. In each subject, k_abs,i_ will be calculated from the slope of the isotopic ratio decrease over the intervention period. k_abs,c_ will also be calculated for the control period (Day 84 and 168). k_abs_ will be modelled using linear mixed models with time (intervention and control period) and treatment as fixed factors and subjects ID as random factors. The time treatment interaction on k_abs_ will be assessed. A similar but separate analysis will be conducted on the total amount of iron absorbed, which will be estimated from the k_abs_ value in each subject, and the group and time effect will be modelled with linear mixed models. The models will be compared to the standard treatment of supplementation with 12 mg iron/day universal.

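### The sub-study model for iron absorption has no Day 0 covariates, which gives up precision in the between-arm comparison

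*Protocol article*

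**What the plan says.** The Sample size section bases the sub-study on absorbed iron in mg/d: "Twenty subjects per group are required to resolve a difference in absorbed iron of 0.080 mg/d between the control and intervention period", with an SD of 0.13 mg/d and a paired t-test. For the unpaired comparison it adds: "The between group difference that we estimate being able to resolve is 0.12 mg/d absorbed iron". Thirty per group are recruited to allow for attrition. It then remarks: "Lower variability is expected in the calculated k_abs_ values, which are independent from Hb, body weight, and iron status". The same sentence goes on to call these three quantities the chief sources of variability when iron absorption is calculated. No SD for k_abs is given.

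Under Statistical analysis, k_abs is the slope of the isotope data alone, and total absorbed iron is then estimated from it. The model is explicit: "k_abs_ will be modelled using linear mixed models with time (intervention and control period) and treatment as fixed factors", with subject as a random factor and a time-by-treatment interaction. A similar model is planned for total absorbed iron. The intervention period is Day 0 to 84; the control period is Day 84 to 168.

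Three other statements bear on this model:
- Recruitment, enrolment and randomisation: allocation is in blocks, balanced by Hb and age.
- Laboratory evaluations: haematology, ferritin, sTfR and hepcidin are measured at Day 0, in sub-study children as well.
- Hepcidin-guided iron supplementation: "hepcidin also determines how well oral iron is absorbed".

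**The concern.** If hepcidin governs absorption, Day 0 hepcidin should predict how much iron a child absorbs over the following weeks. In two of the three arms, weekly hepcidin also decides whether the child receives iron at all. The model nevertheless leaves this predictor and both balancing factors in the residual.

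With about 20 children per arm, between-child variation largely sets what the arm comparison can resolve. The control period cannot stand in for a baseline, because it follows 12 weeks of randomised supplementation and may itself differ by arm. The Background describes the route: "iron accumulation induces hepcidin, providing a negative feedback loop to maintain homeostasis". Only Day 0 values are safely pre-treatment. Choosing covariates after seeing the data would be hard to defend at this size, so the choice belongs in the plan.

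**Working it through.** **Inputs from the protocol article.** n = 20 evaluable per group; SD 0.13 mg/d of absorbed iron; paired difference 0.080 mg/d; between-group difference 0.12 mg/d.

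**Assumptions.** The sub-study calculation states neither alpha nor power. I take two-sided 5 % and 80 %. I also take 0.13 mg/d as the between-child SD within an arm, as the plan's own unpaired figure appears to do.

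**1. Reproducing the plan's figures.**
- Paired, normal approximation: n = ((1.960 + 0.842) × 0.13 / 0.080)² = 20.7, so 21 against the stated 20. An exact t calculation gives 23.
- Unpaired, normal approximation: 0.13 × √(2/20) × 2.802 = 0.115 mg/d. With the noncentral t on 38 df it is 0.118 mg/d, which rounds to the stated 0.12.

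Both figures are met closely enough. Neither uses an SD for k_abs, so neither depends on the remark about lower variability.

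**2. Effect of baseline covariates on the between-arm comparison.** If the covariates explain a share R² of the between-child variance, the residual SD is 0.13 × √(1 − R²) and the detectable difference shrinks by the same factor. R² is an assumed range; the documents give no value.

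| R² | Residual SD (mg/d) | Detectable difference (mg/d) |
|---|---|---|
| 0 | 0.130 | 0.118 |
| 20 % | 0.116 | 0.106 |
| 30 % | 0.109 | 0.099 |
| 40 % | 0.101 | 0.092 |

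**3. Charge for estimating the covariates.** These figures treat the covariate effects as known. With four covariates in a two-arm comparison of 40 children, the error df fall from 38 to 34, and chance imbalance inflates the expected variance by about (38 − 1)/(38 − 4 − 1) = 37/33 = 1.12. The noncentral t then gives 0.112, 0.105 and 0.097 mg/d for R² of 20, 30 and 40 %. In one model for all three arms (57 df before covariates) the inflation is 56/52 = 1.08, and the figures are 0.109, 0.102 and 0.094 mg/d. On variance alone, four covariates break even at an R² of 4/37 = 11 % (two arms) or 4/56 = 7 % (three arms).

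**4. Where the gain does not apply.** In complete data, a Day 0 value entered as a main effect is the same in both periods of a child. It therefore cancels from the within-child change and from the time-by-treatment contrast. The gain is confined to the comparison of arms within the intervention period.

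**The case against.** The strongest objection is that this is a preference and not an error. Allocation is randomised and balanced by Hb and age, so the unadjusted comparison is valid. The within-child contrast already removes stable differences between children. Covariate lists are often left to the analysis plan, and the size of the gain rests on an assumed R². Most of this stands: there is no bias, no gain for the interaction, and no figure in the documents for R². It does not dispose of the point, because the article does not leave the model open. It names the terms, and they omit both the balancing factors and a measured predictor that the trial's own rationale makes central.

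A reader might go further and infer that the independence remark contradicts the trial's premise about hepcidin, so that the sub-study size is unsupported. The documents do not bear this out. Read to its end, the sentence concerns what enters a calculation: k_abs comes from isotope data alone, without Hb, weight or iron-status inputs. That is compatible with absorption depending physiologically on iron status. The 20 per group and 0.12 mg/d already rest on the SD of 0.13 mg/d.

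Nor can it be shown that k_abs must be the more variable measure. Take illustrative CVs of 0.4 for absorption and 0.2 for body iron, uncorrelated. The log-scale variance of k_abs is then 0.16 + 0.04 = 0.20. Calculated absorbed iron has variance 0.16 + e², where e is the CV of the error in the estimated iron pool. The order reverses once e exceeds 0.20, and the documents fix none of these values.

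**Conclusion.** The point holds as one of efficiency. The stated models for k_abs and total absorbed iron omit Hb, age and Day 0 hepcidin, and so give up precision in the between-arm comparison for the intervention period. Under the assumptions above, the detectable difference could fall from 0.118 mg/d to roughly 0.09 to 0.11 mg/d if the covariates explain 20 to 40 % of the variance. Below about 10 % there would be little or no gain. Validity and the stated sample sizes are unaffected.

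The independence sentence is loosely worded, and its expectation of lower variability has no figure behind it. That is editorial: no stated number depends on it.

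**What to change.** In the sub-study part of Statistical analysis, prespecify Day 0 Hb, age, Day 0 hepcidin on the log scale, and at most one further Day 0 iron marker (sTfR or ferritin) as fixed covariates in the between-arm comparison of k_abs and of total absorbed iron. State that the time-by-treatment contrast is not expected to gain from them.

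In Sample size, say that k_abs is calculated without Hb, weight or iron-status inputs, and either delete the expectation of lower variability or support it with an SD for k_abs.

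The cost is a few sentences and three or four degrees of freedom. No new data are needed, and the numbers recruited do not change.
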